The main study hypothesis is that positive communication plus acupuncture (penetrating verum or non-penetrating sham acupuncture) is more effective than neutral communication plus standard care for nausea, calculated as the mean score for the first 5 days of the studied chemotherapy session period. We hypothesize that treatment expectation is a mediator of the effects.

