### Sample Size

Participants will complete the study procedure during a single chemotherapy session, specifically, the next scheduled session following inclusion. The primary outcome is the mean intensity of nausea for the first 5 days, that is, the day of the intravenous chemotherapy session and the 4 following days of the studied chemotherapy session period. We performed an a priori sample size calculation, ensuring the study to be sufficiently powered. Based on previous research,^
15
^ we aimed to detect a clinically important difference of 10 millimeters (mm) using a 100 mm Visual Analog Scale (VAS) nausea measure between the positive and neutral communication group. Assuming a 2-sided alpha of .05 and statistical power of 80%, we estimated that 198 participants (99 per communication style group) would be required. The data analysis will be conducted according to intention to treat. To allow for a potential dropout rate of 20% between inclusion and the study procedure, the study will recruit up to 240 patients.

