### Data Analysis Plan

The intention-to-treat principle will be applied when analyzing the study data, that is, all patients will be analyzed as randomized, regardless of whether they complete the study procedure as planned. The primary parameters of interests are the 2 factorial effects (2 main effect, ie, 1. communication style, and 2. treatment type, and one interaction, ie, treatment expectations) during the first 5 days of the studied chemotherapy session period. The evaluator will use a generalized linear mixed effects model (GLMM) to determine if the independent variables communication style and treatment type affect the dependent variable nausea. We take the stratified randomization into account (adjusting for random effects of department on the outcomes) and include baseline characteristics in the analysis model to increase the precision of the estimates.^
77
^ In secondary GLMMs, we will study the effects of the variety of independent variables on vomiting, QoL, and daily and physical activity. Patients who cease to participate (dropouts) and missing data will be handled according to routines as follows. In the main analysis, missing data will be handled using multiple imputations by chained equation.^
78
^ We will specify the multiple imputation model (the choice of auxiliary variables) after comparing patient characteristics between those with complete and those with incomplete data. Under the assumption that data are missing at random, an analysis based on multiple imputation conforms with the intention to treat. We will then also estimate the factorial effects using complete data only. We will conduct a sensitivity analysis by comparing estimates regarding the 2 main effects described above with estimates based on complete data only, in other words, a pattern-mixture model and tipping point analyses. Statistical significance will be defined as a 2-tailed *P* < .05, and the analyses will be performed in IBM SPSS statistics (IBM Corp, Armonk NY, USA).

In line with previous recommendations regarding cost-effectiveness analysis alongside clinical trials, we will specify the methods for cost effectiveness analysis after evaluating these outcomes. If the present evaluation shows significant health benefits on the primary outcome measure, or in at least on 1 secondary outcome, a cost-effectiveness analysis of our intervention will be conducted using a model-based approach.^
79
^

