[Bibr bibr7-15347354251361464][Bibr bibr8-15347354251361464]-9^ facilitated daily and physical activity,^7,10^ and perhaps a reduced need for rescue antiemetics.^
76
^ This in turn may result in lower burden on the healthcare system and reduced societal costs,^11,12^ thus positively affecting public health. Health economic evaluations of integrative interventions regarding effects of non-specific treatment components, sometimes cited as “placebo effects,” are scarce.^
52
^

Important aspects of the study plan are the randomized controlled design, and the accurate collection of data needed to be able to control for potential confounding factors. Although the main aim of the present effectiveness study is to compare different communication styles and to compare verum acupuncture with sham acupuncture, one important methodological choice was also to include a third treatment type group, that is, the standard care group. In line with recommendations for research on contextual effects,^
83
^ this allows us to compare how much additional nausea-reducing effect positive communication and acupuncture may have, if any, compared to the standard care that all patients receive in routine clinical practice. Given the strong evidence showing that pharmacological antiemetic therapy is beneficial for persons undergoing emetogenic chemotherapy,^1
[Bibr bibr2-15347354251361464][Bibr bibr3-15347354251361464]-4,14^ we considered it unethical to randomize persons to an untreated control group that would not be offered any antiemetic therapy at all. Accordingly, all patients receive standard care, and the verum and sham acupuncture and communication styles are conducted in addition to standard care. Patients randomized to standard care combined with neutral communication receive treatment that is comparable to the treatment given in clinical standard care. To succeed with the challenge of blinding patients, the study uses the credible^
59
^ telescopic Park et al’s sham device^
58
^ in the sham acupuncture group. Patients, acupuncture-experienced patients included, could not distinguish if they received verum acupuncture to PC6 or sham acupuncture, using that device.^
59

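### The declared main hypothesis is neither the comparison that the 198 patients were sized for nor a listed primary parameter, so 80% power is shown only for communication style

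*Protocol article*

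**What the plan says.** Write 1 and 2 for neutral and positive communication, and A, B and C for standard care, sham and verum acupuncture. Four places in the protocol article say what the trial is mainly about.

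- **Introduction, last paragraph.** The hypothesis labelled as the main one reads: "positive communication plus acupuncture (penetrating verum or non-penetrating sham acupuncture) is more effective than neutral communication plus standard care". Its endpoint is mean nausea over the first five days, which is the primary outcome. This is 2B and 2C against 1A.
- **Sample Size.** The target is 10 mm on the "Visual Analog Scale (VAS) nausea measure between the positive and neutral communication group". With two-sided alpha .05 and 80% power, "we estimated that 198 participants (99 per communication style group) would be required". This is style 2 against style 1, pooled over A, B and C. The section says that the calculation makes the study sufficiently powered. It gives no SD.
- **Data Analysis Plan.** "The primary parameters of interests are the 2 factorial effects", spelled out as the main effects of communication style and treatment type, plus an interaction that is glossed as treatment expectations. The 2B and 2C versus 1A contrast is not listed.
- **Discussion.** "the main aim of the present effectiveness study is to compare different communication styles and to compare verum acupuncture with sham acupuncture".

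The Figure 1 caption states roughly equal allocation to the arms.

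**The concern.** The sentence labelled as the main hypothesis names the primary endpoint, so a reader will take it as the confirmatory claim. Yet it has no effect size, no power and no place among the primary parameters. The assurance about power belongs to another comparison.

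Interpretation is also at stake. Under The Communication Model, the therapist's visit in 1A is meant to be brief and close to routine care. Patients in B and C have two 20-minute needling sessions. Patients in A know that they had no needles: the blinding question gives them a not-applicable answer. A difference between 2B and 2C and 1A therefore combines communication, needling, contact time and awareness of treatment. The closing statements of the Abstract and the Discussion would use a positive trial to bring the communication model into routine care. This contrast alone could not support that step.

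**Working it through.** **Inputs.** From Sample Size: difference 10 mm, two-sided alpha .05, power 80%, 99 per style. From the equal allocation in Figure 1: 198/6 = 33 expected per arm, so 2B + 2C = 66 and 1A = 33. Randomization is not blocked, so these are expected numbers. The SD is not stated and is back-solved below. Using 10 mm for the hypothesis contrast is an assumption, because the plan sets 10 mm for communication only.

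**1. The plan's own figure.** For two means, the detectable difference is (1.960 + 0.842) × SD × √(1/n₁ + 1/n₂).

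- SD = 10 / (2.802 × √(2/99)) = 25.1 mm by the normal approximation, or 25.0 mm by the t test.
- At SD 25, 99 v 99 has 80.4% power (normal) or 80.0% (noncentral t).

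The 198 is coherent with an SD of about 25 mm. It cannot be confirmed independently.

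**2. The main hypothesis, 66 v 33, SD 25.**

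- Standard error = 25 × √(1/66 + 1/33) = 5.33 mm.
- Power at 10 mm = Φ(10/5.33 − 1.960) = Φ(−0.084) = 46.7%; noncentral t, 45.9%.
- Difference for 80% power = 2.802 × 5.33 = 14.9 mm; noncentral t, 15.1 mm.

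| True difference | Power, 66 v 33, SD 25 (noncentral t) |
|---|---|
| 10 mm | 46% |
| 12.5 mm | 64% |
| 15 mm | 80% |

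The result hardly depends on the back-solved SD. The ratio of the two standard errors is √[(1/66 + 1/33)/(2/99)] = √2.25 = 1.5. Whatever common SD gives 80% power for 10 mm at 99 v 99, the 66 v 33 contrast needs 15 mm for the same power. At 10 mm its power is Φ(2.802/1.5 − 1.960) = 46%. If the SD is instead fixed at 24 or 26 mm, the power is 49% or 43%.

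**3. Variants.**

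- 2B and 2C each tested separately against 1A (33 v 33, 10 mm): 36%. The hypothesis does not say whether they are pooled.
- All 240 recruits analysed (80 v 40, 10 mm): 54%.
- Verum versus sham over both styles (66 v 66, SD 25): 63% at 10 mm, and 80% at about 12.3 mm.

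**The case against.** **The plan is more consistent than it may look.** A reader might infer that the hypothesis, sample size and analysis describe three unrelated comparisons. They do not. Communication style is the powered contrast, the first primary parameter and the first half of the Discussion's main aim. Verum versus sham is a component of the treatment-type effect. The hypothesis sentence is the outlier. This stands, and it makes the repair simpler.

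**The 46% is conditional.** The hypothesis contrast differs on both factors. If their effects add and communication is worth 10 mm, 46% is the power when acupuncture adds nothing; a further 5 mm restores 80%. This also stands: a reader may not conclude that the trial has 46% power for its main hypothesis. But the plan states neither 10 mm nor any larger difference for this contrast, so no power is shown for it. Adjustment for baseline characteristics could raise power, but it would help every contrast, and the plan's figure of 198 does not mention it.

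**The article is condensed.** A model with both factors can produce the 2B and 2C versus 1A contrast, and test hierarchy is commonly left to an analysis plan. A reader might infer an inflated familywise error, or that the confirmatory result could be picked after seeing the data. The article does not fix the set of tests closely enough to support either inference, and its silence on hierarchy is no finding. What remains is what the article does state: the main hypothesis and the primary parameters differ, and an analysis plan cannot follow both as written.

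**Attribution.** The mixing of components affects only the hypothesis contrast. The communication main effect compares styles with treatment type balanced, so it can be credited to communication. Keeping standard care as a reference is a deliberate choice that the Discussion explains.

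**Conclusion.** The plan is wrong as written on this point, and wording can repair it. The main hypothesis is neither the comparison that was powered nor one of the primary parameters, and the Discussion adds verum versus sham as a main aim. The claim of sufficient power is shown only for positive versus neutral communication.

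For the hypothesis contrast, power is about 46% if the difference is also 10 mm and the SD is about 25 mm, and 80% at about 15 mm. This rests on 33 patients per arm, a common SD, 2B and 2C pooled, and no covariate adjustment. The 10 mm is borrowed from the communication comparison, and the true difference could be larger if acupuncture contributes.

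**What to change.** Before unblinding:

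1. Name one primary test: positive versus neutral communication on the 5-day mean VAS nausea score, two-sided .05. This is the comparison that 198 patients support.
2. Reword the main hypothesis in the Introduction to match, and align the primary parameters in the Data Analysis Plan and the main aim in the Discussion.
3. State the SD behind the 198.
4. List 2B and 2C versus 1A, and the treatment-type contrasts including verum versus sham, as secondary. Give detectable differences at 80% power with SD 25: about 15 mm for the first and about 12.3 mm for verum versus sham.

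If the authors prefer to keep 2B and 2C versus 1A as the main hypothesis, they should add it to the analysis section, say whether the two arms are pooled, and restate its power as about 46% at 10 mm and 80% at about 15 mm.

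No extra patients or data are needed. The cost is a documented amendment to a declared main hypothesis while the trial is recruiting, and less favourable stated power for the secondary contrasts.

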## Methods

### Design

The study uses a randomized sham-controlled design. The design is a 2 × 3 factorial design^
53
^ where patients are randomized to the communication styles 1. neutral communication, or 2. positive communication, given when undergoing 1 of 3 antiemetic treatments (Figure 1). All patients receive standard care; patients randomized to antiemetic treatment type B (sham acupuncture), or C (verum acupuncture) receive the acupuncture therapy in addition to A (standard care). The structure of the intervention follows the Template for Intervention Description and Replication (TIDieR) checklist^
54
^ and the Standard Protocol Items: Recommendations for Interventional Trials (SPIRIT).^
55
^

**Figure 1. fig1-15347354251361464:**
[figure not shown]
Flow chart of patient inclusion and allocation groups. The intended distribution is 1:1, meaning approximately equal numbers will be allocated to each arm.

The study was approved by the Regional Ethical Committee (Umeå 2016/362-31, and Umeå 2017/488-32) and trial registration was conducted preceding the inclusion of the first participant.

### Sample Size

Participants will complete the study procedure during a single chemotherapy session, specifically, the next scheduled session following inclusion. The primary outcome is the mean intensity of nausea for the first 5 days, that is, the day of the intravenous chemotherapy session and the 4 following days of the studied chemotherapy session period. We performed an a priori sample size calculation, ensuring the study to be sufficiently powered. Based on previous research,^
15
^ we aimed to detect a clinically important difference of 10 millimeters (mm) using a 100 mm Visual Analog Scale (VAS) nausea measure between the positive and neutral communication group. Assuming a 2-sided alpha of .05 and statistical power of 80%, we estimated that 198 participants (99 per communication style group) would be required. The data analysis will be conducted according to intention to treat. To allow for a potential dropout rate of 20% between inclusion and the study procedure, the study will recruit up to 240 patients.

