### Randomization and Blinding

Using a computerized randomization table, a statistician randomizes the patients, stratified for hospital, to 1 of the 2 communication styles (1 or 2) conducted during 3 treatment types (Type A, B, or C; Figure 1) without applying any block randomization. After the intervention therapist initially conducts the physiological measures described below, he/she receives the randomization result from the randomization table and begins the study procedure in line with the randomization result (Figure 2), according to a standardized treatment protocol. The patients and all medical and healthcare personnel, other than the intervention therapist delivering the standardized treatment protocol procedures, are blinded to the acupuncture and communication allocation (see description of treatment types below). The evaluator is blinded to allocation until after analysis of the primary outcome. This is possible because all patients and allocation groups are coded; the evaluator does not know which code means which allocation group until thereafter.

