Self-reported descriptive data: On a baseline questionnaire, patients supply sociodemographic data (eg, sex, age, level of education, profession), clinical data (eg, comorbidities, disease-specific variables, medications), data on previous experience of and belief in acupuncture effects,^
22
^ data on previous nausea experiences in their lives and specifically when undergoing cancer therapy, self-predicted risk for nausea,^
36
^ and data regarding therapeutic alliance, for example, to which extent the patient trusts the therapist to be able to help him/her.^
61
^

Data on nausea and vomiting: Patients complete a measure of nausea and vomiting^
7
^ daily for 10 days, answering questions about the primary outcome (nausea intensity) and the secondary outcomes (nausea occurrence, duration of nausea, vomiting episodes, and consumption of antiemetics). This measure asks the following questions with reference to the past 24 hours: “Have you experienced nausea?” (“No” / “Yes”); “How intense was the nausea?” A 100 mm VAS with verbal anchors “No nausea” and “Worst possible nausea” is used. The accumulated duration (in minutes) of nausea within the past 24 hours is registered. Patients also respond to the questions: “Have you vomited?” (“No”/“Yes”), “How many episodes?” (number of episodes is given), and “Have you consumed rescue antiemetics?” (“No”/“Yes”). They are asked to: “Please detail agent, dose and frequency of each antiemetic agent used.” Also, other kinds of nausea and vomiting-related care consumption is self-registered. Burden is asked for and registered on 2 separate 100-mm VAS: “Did the nausea negatively affect your daily life?.” The same question is posed regarding vomiting, both anchored with 0 (“Not affected at all”) and “100” (“Affected in the worst possible way”; Figure 2).

Expectations data: Patients rate their treatment expectations daily for 10 days, using a valid expectancy measure,^
56
^ “Do you believe that the treatment you are going to receive is effective for nausea and vomiting?” This is measured using a 100 mm VAS anchored with 0 (“I don’t believe at all that it’s effective”) and 100 (“I completely believe that it’s effective”). Post-treatment, the question is written with the modified verb tenses “received” and “was.”

Treatment satisfaction data: On day 10 after the intervention, patients rate their interest in receiving future acupuncture treatment by answering the questions^
37

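### Recruiting up to 240 patients does not cover the stated 20% dropout: 192 would remain where 198 are required, and 240 covers only 17.5%

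*Protocol article*

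**What the plan says.** The Sample Size section gives the target difference ("we aimed to detect a clinically important difference of 10 millimeters (mm) using a 100 mm Visual Analog Scale (VAS) nausea measure"), the error rates ("Assuming a 2-sided alpha of .05 and statistical power of 80" per cent) and the result: "we estimated that 198 participants (99 per communication style group) would be required". It gives no SD. The allowance for losses follows: "To allow for a potential dropout rate of 20% between inclusion and the study procedure, the study will recruit up to 240 patients". The Abstract repeats 198 as the calculated size, and no other section gives a different recruitment number or corrects this one. The legend to Figure 1 adds the allocation ratio: "The intended distribution is 1:1, meaning approximately equal numbers will be allocated to each arm".

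**The concern.** Three printed figures (198 required, 20% lost, at most 240 recruited) must satisfy one equation, and they do not. To keep 198 after losing a fifth, 198 must be divided by 0.8. Multiplying 198 by 1.2 always gives too few, because the 20% loss applies to the larger recruited number and not to the 198. Since 240 is worded as a ceiling, the text leaves no room to make up the difference. What is at stake is whether the size that the article presents as sufficient matches its own dropout assumption.

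**Working it through.** **Inputs from the Sample Size section:** required N = 198 (99 per group); dropout d = 0.20; ceiling = 240; difference = 10 mm; two-sided alpha 0.05; power 80%. **From the Figure 1 legend:** 1:1 allocation. **Not in the article:** the SD.

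**1. Reproducing 240.**
- Mark-up, N × (1 + d): 198 × 1.2 = 237.6, so 238, which rounds up naturally to 240.
- Division, N / (1 − d): 198 / 0.8 = 247.5, so 248 (124 per communication style).

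The printed figure is close to the first and 8 below the second. That it came from the mark-up is an inference; the article does not show the step.

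**2. What 240 delivers.**
- Remaining after 20% loss: 240 × 0.8 = 192, or 96 per group with an equal split.
- Shortfall: 198 − 192 = 6 patients, or 6 / 198 = 3.0%.
- Largest dropout that still leaves 198: 1 − 198 / 240 = 0.175, or 17.5%.

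Nothing so far needs an assumption.

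**3. Effect on power (needs an assumed SD).** Back-solving from 99 per group with the normal approximation:

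SD = 10 × √(99/2) / (1.960 + 0.842) ≈ 25.1 mm.

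Power at 96 per group is Φ(10 / (25.11 × √(2/96)) − 1.960) = Φ(2.759 − 1.960) = Φ(0.799) ≈ 78.8%. With the noncentral t distribution and SD 25 mm, power is 79.97% at 99 per group and 78.7% at 96. Either way the loss is about 1.2 percentage points.

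The size of the loss depends little on the SD (normal approximation):

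| Assumed SD (mm) | N per group for 80% power | Power at 99 per group | Power at 96 per group |
|---|---|---|---|
| 24 | 91 | 83.4% | 82.3% |
| 25 | 99 | 80.4% | 79.1% |
| 25.1 | 99 | 80.0% | 78.8% |
| 26 | 107 | 77.2% | 76.0% |

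Of these, only SDs of 25 and 25.1 mm return the article's 99 per group. In every row the cost of 96 against 99 is between 1.1 and 1.3 points.

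**The case against.** The strongest reply is that this hardly matters. The article calls the 20% a potential rate, 240 covers 17.5%, and six patients is 3% of the target. The power figures above are also for an unadjusted comparison, whereas the Data Analysis Plan specifies a mixed model that adjusts for baseline variables to gain precision. If 198 is an unadjusted figure, covariates explaining about 3% of the outcome variance (1 − 192/198) would offset the shortfall. The article gives no such proportion, so this is only an illustration. The reply stands as to size: a reader might infer that the trial will miss its 80% power, and the article does not establish that. It does not make the sentence about 240 correct.

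Two stronger readings are tempting, and neither is supported.

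- **No provision for outcome data lost after the procedure.** The 20% is expressly limited to losses before the procedure, and no second allowance is printed. But this is a condensed article, which may leave such an allowance to the full protocol, and it gives no rate of diary loss, so any power figure for that loss would rest on invented rates. The Data Analysis Plan does deal with missing outcomes: "In the main analysis, missing data will be handled using multiple imputations by chained equation", with sensitivity analyses alongside. The primary outcome is a five-day mean, so a patient who misses a day or two is not wholly lost.
- **The 20% loss all falls before randomisation.** Randomization and Blinding says of the intervention therapist that "he/she receives the randomization result from the randomization table and begins the study procedure in line with the randomization result". That fixes when the allocation is revealed, not when it is made, since a statistician holds the table. The timing of randomisation is therefore open. The dropout arithmetic does not depend on it.

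**Conclusion.** The point holds as an arithmetic error in a stated size. On the article's own figures, 240 does not allow for 20% dropout: it leaves 192, not 198, and covers 17.5%. Dropout of 20% implies 248. That conclusion rests on no assumption. The cost of about 1.2 power points, to about 79%, rests on an SD of about 25 mm back-solved from 99 per group, on an equal split and on an unadjusted two-group comparison. The error is minor. It does not show that the trial is underpowered under its planned analysis.

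**What to change.** Correct the last sentence of the Sample Size section in one of two ways.

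- **Keep the ceiling and restate what it covers.** Suggested wording: *Up to 240 patients will be recruited, which allows for 17.5% dropout before the study procedure. At 20% dropout about 192 would undergo it, giving about 79% power for an unadjusted two-group comparison, assuming an SD of about 25 mm.* The authors should put in the SD they actually used and recompute the power if it differs. The cost is a slightly less favourable printed figure and no extra patients.
- **Keep the 20% and restate the number.** Give 248 as the recruitment figure that 20% dropout implies. The cost is up to 8 more patients than the present ceiling (248 − 240).

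Either is enough. The first is the cheaper, as recruitment is described as already under way.
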